## Abstract

**Background:**

Regular exercise has been shown to have beneficial health effects in cancer survivors, including improving quality of life and other important health outcomes. However, providing people with cancer with easily accessible, high-quality exercise support and programs is a challenge. Therefore, there is a need to develop easily accessible exercise programs that draw upon the current evidence. Supervised, distance-based exercise programs have the benefit of reaching out to many people whilst providing the support of an exercise professional. The aim of the EX-MED Cancer Sweden trial is to examine the effectiveness of a supervised, distance-based exercise program, in people previously treated for breast, prostate, or colorectal cancer, on health-related quality of life (HRQoL), as well as other physiological and patient-reported health outcomes.

**Methods:**

The EX-MED Cancer Sweden trial is a prospective randomised controlled trial including 200 people that have completed curative treatment for breast, prostate, or colorectal cancer. Participants are randomly allocated to an exercise group or a routine care control group. The exercise group will participate in a supervised, distanced-based exercise program delivered by a personal trainer who has undertaken specialised exercise oncology education modules. The intervention consists of a combination of resistance and aerobic exercises with participants completing two 60-min sessions per week for 12 weeks. The primary outcome is HRQoL (EORTC QLQ-C30) assessed at baseline, 3- (end of intervention and primary endpoint) and 6-months post-baseline. Secondary outcomes are physiological (cardiorespiratory fitness, muscle strength, physical function, body composition) and patient-reported outcomes (cancer-related symptoms, fatigue, self-reported physical activity), and self-efficacy of exercise. Furthermore, the trial will explore and describe the experiences of participation in the exercise intervention.

**Discussion:**

The EX-MED Cancer Sweden trial will provide evidence regarding the effectiveness of a supervised, distance-based exercise program for survivors of breast, prostate, and colorectal cancer. If successful, it will contribute to the implementation of flexible and effective exercise programs as part of the standard of care for people following cancer treatment, which is likely to contribute to a reduction in the burden of cancer on the individual, health care system and society.

**Trial registration:**

www.ClinicalTrials.gov NCT05064670. Registered on October 1, 2021.

## Background

There is now robust evidence showing that both aerobic and resistance exercise plays an important role in improving the quality of life, psychological health, and physical function, as well as helping to manage common cancer-related side effects, among people who have completed cancer treatment [1–5]. International health organisations are therefore calling for exercise to be incorporated into routine cancer care [6–8]; however, the great challenge in the field of exercise oncology is being able to provide people with cancer easily accessible, high-quality exercise support and programs. Consequently, there is an urgent need to develop exercise programs that draw upon the current evidence base that can be delivered to as many people as possible.

In recent years, particularly in light of a major pandemic, there has been an increase in distance-based delivery of health care in an attempt to improve supportive care services for people with cancer [9, 10]. Interventions such as symptom monitoring and management, remote rehabilitation program delivery, nursing support, health education, and psychotherapy are provided using digital technologies including telephones or smartphones, video, and web-based portals [9, 11]. Although much of health care delivery still occurs face-to-face, distance-based interventions have been shown to improve health-related outcomes, such as health-related quality of life (HRQoL), functional capacity, and cancer-related symptoms [9, 11]. Additionally, distance-based interventions are now much more accepted, are clinically safe, and have the major advantage of reducing the impact on a person’s daily activities, for example by minimising the burden of travel [12–14].

The original EX-MED Cancer program (exercise medicine program for people with cancer) [15], a supervised, facility-based exercise program, was developed, trialled, and implemented in Australia to incorporate best practice evidence-based exercise prescription whilst minimising burden to patients and health care professionals [16]. It capitalises on existing community-based workforce and resources, to facilitate widespread participation by cancer survivors, scalability, and sustainability of the program with the goal of embedding exercise medicine into routine cancer care. EX-MED Cancer Sweden has been adapted from the Australian model to a distance-based exercise program. Supervised, distance-based exercise programs have the benefit of reaching out to as many people as possible, allowing participants to exercise at home, avoiding public places and travel, whilst still gleaning the benefits of supervision by a trained fitness professional [17, 18]. Additional commonly identified facilitators of exercise among cancer survivors include group-based exercise with other cancer survivors, and exercise that is individually tailored, varied, and gradually progressive with individual feedback [17, 18].

Whilst the EX-MED Cancer program has been successfully implemented in Australia, no similar program exists or has been trialled in Sweden. EX-MED Cancer Sweden is a single-centre phase 3 randomised controlled trial. It aims to examine the effectiveness of a supervised, distance-based exercise program, in people previously treated for breast, prostate, or colorectal cancer, on HRQoL, as well as other physiological and patient-reported health outcomes. Additionally, we aim to explore and describe the experiences of participation in the exercise program, to inform further design and implementation of exercise programs for cancer survivors.

## Methods and design

EX-MED Cancer Sweden is a prospective superiority two-armed single-centre randomised controlled trial, testing a supervised, distance-based physical exercise intervention for survivors of breast, prostate, or colorectal cancer (Table 1 and Fig. 1). The trial is based on the EX-MED Cancer trial, ongoing program and professional development course originally developed and implemented in Australia [15, 16, 19]. The primary outcome is HRQoL. Secondary outcomes are physiological (cardiorespiratory fitness (CRF), muscle strength, physical function, body composition) and patient-reported outcomes (cancer-related symptoms, fatigue, self-reported physical activity), and self-efficacy of exercise. Furthermore, the trial will explore and describe the experiences of participation in the exercise intervention.

**Table 1 Tab1:**
[figure not shown]
Schedule of enrolment, interventions, and assessments for the EX-MED Cancer Sweden trial

*HRQoL* Health-related quality of life, *CRF* Cardiorespiratory fitness

*Only for the exercise group

**Fig. 1 Fig1:**
[figure not shown]
Schematic flow diagram of the EX-MED Cancer Sweden trial

### Study setting

The exercise lab at The Karolinska Comprehensive Cancer Centre, Stockholm, Sweden, is responsible for the coordination of EX-MED Cancer Sweden. It is the central point of contact for study participants and health care professionals and where testing will be conducted. Study participants will exercise in their own homes, or other suitable locations, using the online platform Microsoft® Teams, where a personal trainer will be the host and supervisor for the session.

### Population

People diagnosed with any type of stage I–IIIa breast, prostate, or colorectal cancer who have undergone and completed curative treatment in the last five years whilst fulfilling all inclusion criteria are eligible to participate in the trial (Table 2). People are eligible if they are currently receiving or are scheduled to receive anti-hormonal therapy. Informed consent is required before baseline testing and will be obtained by a nursing member of the research team.

**Table 2 Tab2:** Inclusion and exclusion criteria in the EX-MED Cancer Sweden trial

Inclusion criteria	Exclusion criteria
• Age ≥ 18 years • Diagnosed with any type of stage I–IIIa breast, prostate or colorectal cancer • Undergone and completed curative treatment (eligible if currently receiving/scheduled to receive anti-hormonal therapy) within the last 5 years at the Karolinska Comprehensive Cancer Centre, Sweden	• Currently receiving or scheduled to receive cancer treatment (except anti-hormonal therapy) • Any medical conditions that may prevent safe participation in the testing or exercise demands of the study [20] • Performing regular exercise throughout the last month defined as undertaking at least 150 min moderate-intensity aerobic exercise and two or more structured resistance exercise sessions per week • Unable to read and speak Swedish

A selection of people participating in the exercise intervention and the personal trainers, employed at the gym franchise SATS, will be recruited to a qualitative study exploring and describing experiences of participation in the intervention.

### Intervention

All participants will undergo baseline testing of physical fitness and strength prior to randomisation. Participants randomised to the intervention will be registered for the next exercise group to commence within 2 weeks of baseline testing. Participants will complete two 60-min distance-based exercise sessions per week for 12 weeks (24 sessions in total). The program consists of a combination of resistance and aerobic exercises. The exercise sessions are delivered by upskilled personal trainers in groups of up to eight people. Educational modules have been developed for the personal trainers and are delivered by the research group prior to delivering the intervention. These modules are the EX-MED Cancer PD course [19], developed in Australia by author PC, with modifications made to contextualise the content to the Swedish healthcare setting. Modules consist of an introduction to cancer, side effects of cancer treatments, screening and monitoring of cancer, exercise prescription for cancer and working with people with cancer. Prior to commencing the exercise intervention, participants will receive an in-person familiarisation of the exercise program from a member of the research team. They will be provided with a hard copy of the exercise program, resistance bands for training, a detailed information booklet about exercise for people with cancer, and a logbook to record attendance, exercise adherence and level of exertion. Any barriers to exercise identified by the participant or the research team will also be discussed, and solutions developed together.

The exercise intervention is a progressive circuit training program consisting of a consecutive series of timed exercises performed one after the other. Incorporating whole-body functional exercises, sessions include four blocks with three exercises per block, including two whole-body resistance-focused and one aerobic-focused. Each set of three exercises will be performed for a prescribed amount of time with the participant completing as many repetitions as possible in this time. Each exercise is followed by a short rest interval with a longer rest interval after each set. Each set will be repeated three times before moving on to the next block containing three new exercises. Intensity will be manipulated by using body weight and two different resistance bands, light and medium, and by the participant increasing or decreasing the number of repetitions performed during the prescribed time. Each session will include a warmup and cooldown. The personal trainer will monitor each participant during the sessions to ensure exercises are performed correctly and safely. Exercise prescription is progressive and will be modified by the personal trainer according to individual response. The personal trainer will support the participants to achieve an overall exercise intensity of 14–18 on Borg’s Rating of Perceived Exertion (RPE) scale. Participants will be encouraged to perform at least 150 min of moderate physical activity per week, inclusive of the exercise intervention sessions.

Following the completion of the exercise intervention, immediately after the completion of the post-intervention testing session, participants will receive a written Physical Activity on Prescription (PAP) and be encouraged to continue to exercise. The individualised PAP is a written prescription provided by a registered healthcare professional that prescribes physical activity outside of healthcare services, with the aim of increasing levels of physical activity and integrating it into everyday life [21]. They will be given the opportunity to discuss any goals, preferences, or barriers to future exercise. Participants will not receive any contact or exercise support in the 3-month follow-up period following the initial 3-month intervention.

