### Control

As the aim of the trial is to compare the effectiveness of the exercise program with routine care, the control group is a routine care control group. This means that study participants will receive routine care according to national guidelines [22], which does not involve a standardised, structured exercise program, but may include information and advice about physical activity from the treating nurse, physician or physiotherapist.

At the completion of the trial, following the 6-month post-baseline (follow-up) testing session, the study participants in the control group will be offered a home exercise program, a written PAP, and the same exercise information booklet the exercise intervention group was given. In addition, they will also be offered a hard copy of the same exercise program used in the intervention, including pictures and instructions for the exercises.

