### Sample size

We aim to include 200 participants in this trial. Sample size calculations have been based on having sufficient power to detect a medium effect size (Cohen’s *d* = 0.5) for the primary endpoint, overall patient-reported HRQoL post-intervention. We regard an improvement in HRQoL in the intervention arm from baseline to three months post-baseline relative to the control arm to be of relevance. With a power of 80% and an alpha of 5% (two tailed) from pre- to post-intervention, a total of 160 participants needs to be included; 80 in each arm.

To ensure sufficient participant numbers at the completion of the trial, sample size calculations account for a 20% attrition rate, leading to a total sample size of 200 participants.

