### Assignment of interventions

After the completion of baseline testing, study participants will be randomised by a member of the research team on a 1:1 basis in block samples, using the computer-generated randomisation program ALEA. Randomisation will be stratified by disease type (breast, prostate or colorectal) and treatment with chemotherapy (yes or no). Study investigators and participants will be blinded to group allocation at baseline, but not at the subsequent testing timepoints. The design is open label so unblinding will not occur.

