### Statistical methods

Analyses will be performed using an intention-to-treat approach. For the quantitative analysis, descriptive statistics will be used to describe baseline characteristics. Analysis of covariance (ANCOVA) and linear mixed modelling will be used to detect any significant differences between the two groups at three and six months, respectively. Corresponding effect sizes will also be calculated. Explorative sub-analysis by cancer type will be conducted to investigate if any effects of the exercise intervention are cancer type specific.

For the qualitative analysis, focus group discussions/individual interviews will be transcribed verbatim and analysed using qualitative content analysis.

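### The exercise arm trains in trainer-led groups, but the ANCOVA named for the 3-month primary endpoint has no group or trainer term, so type I error exceeds 5% if outcomes correlate within groups

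*Protocol article*

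**What the plan says.** Allocation is individual. Under Assignment of interventions, "study participants will be randomised by a member of the research team on a 1:1 basis in block samples".

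Delivery is in groups in one arm only. Under Intervention, "The exercise sessions are delivered by upskilled personal trainers in groups of up to eight people", for 24 sessions over 12 weeks. Groups form by time of enrolment: "Participants randomised to the intervention will be registered for the next exercise group to commence within 2 weeks of baseline testing". Under Control, the comparator is routine care, "which does not involve a standardised, structured exercise program".

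The analysis is set out under Statistical methods: "Analysis of covariance (ANCOVA) and linear mixed modelling will be used to detect any significant differences between the two groups at three and six". The sentence assigns the two methods to the two time points in that order, so ANCOVA is the method for the 3-month primary endpoint. No exercise-group or trainer term is named.

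Under Sample size, the inputs are "sufficient power to detect a medium effect size (Cohen’s *d* = 0.5) for the primary endpoint", then "With a power of 80% and an alpha of 5% (two tailed) from pre- to post-intervention". The stated result is: "a total of 160 participants needs to be included; 80 in each arm". A 20% attrition allowance takes this to 200. No ICC, design effect, number of groups or number of trainers is given.

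**The concern.** Participants in the same exercise group share sessions, peers and a trainer who adjusts the programme. The Background section itself lists exercising with other survivors as a facilitator, so peer influence is part of the rationale. The primary endpoint is self-reported quality of life at the end of the intervention, when that shared exposure is complete. Some positive within-group correlation is plausible in the exercise arm and has no counterpart among controls.

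An ANCOVA in its usual form assumes independent residuals. With positive correlation, the exercise-arm mean is less precise than that model reports. The confidence interval is then too narrow and the p-value too small, an error that favours a claim of superiority. Leaving a design effect out of the sample size is a different matter: it affects power, not type I error.

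**Working it through.** **Inputs from the protocol article:** groups of at most 8, exercise arm only (Intervention, Control); d = 0.5, 80% power, two-sided 5%, 80 per arm analysed, 200 recruited (Sample size).

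**Assumptions:** ICC from 0 to 0.10, since none is given; equal group sizes; equal total variance in the two arms; no further correlation from trainers who lead several groups. For the ANCOVA, the relevant ICC is that of the baseline-adjusted outcome.

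**Step 1: the plan's own figure.** The normal formula gives 2 × (1.960 + 0.842)² / 0.5² = 62.8, so 63 per arm (126 in total). The t-based version gives 64 per arm (128). The stated 80 per arm is not reproduced; 80 per arm gives about 88% power. The figure 160 equals 128 / 0.8, and 160 / 0.8 = 200, so the 20% inflation appears to have been applied twice. That is a separate discrepancy. It matters here because it leaves a margin of 160 / 128 = 1.25.

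**Step 2: effect on the standard error.** With m analysed per group:
- exercise-arm design effect: DE = 1 + (m − 1) × ICC
- average over both arms: A = (DE + 1) / 2
- true SE / naive SE = √A
- type I error of the unadjusted test = 2 × [1 − Φ(1.96 / √A)]

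Example, m = 8 and ICC 0.05: DE = 1 + 7 × 0.05 = 1.35; A = 1.175; √A = 1.084; 1.96 / 1.084 = 1.81; type I error 7.1%.

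**Step 3: full groups (m = 8).** The simulation used 20,000 trials of 10 groups of 8 against 80 controls. Adjusted power is for an analysis that allows for the groups. The simulated version uses group means with Satterthwaite degrees of freedom.

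| ICC | A | Type I, formula | Type I, simulated | Adjusted power, formula | Adjusted power, simulated |
|---|---|---|---|---|---|
| 0 | 1.000 | 5.0% | 5.1% | 89% | 86% |
| 0.01 | 1.035 | 5.4% | 5.4% | 87% | 85% |
| 0.02 | 1.070 | 5.8% | 5.7% | 86% | 84% |
| 0.05 | 1.175 | 7.1% | 6.8% | 83% | 80% |
| 0.10 | 1.350 | 9.2% | 9.0% | 78% | 74% |

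**Step 4: smaller groups.** Eight is a maximum. If 100 are allocated to exercise, 100 / 8 = 12.5, so at least 13 groups. With 80 analysed, 80 / 13 is about 6.2 per group. Type I error is then 6.5% at ICC 0.05 (A = 1.13) and 8.1% at ICC 0.10 (A = 1.26). With groups of 2.5 it is 5.1% at ICC 0.01 and 5.9% at ICC 0.10.

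**Step 5: how much clustering 160 analysed can absorb.** Setting A = 1.25 gives DE = 1.5 and, with m = 8, ICC = 0.5 / 7 = 0.071. Measured against the unrounded normal-formula requirement of 62.8 per arm, the limit is 0.078. With small-sample degrees of freedom, simulated power is already about 80% at ICC 0.05.

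**The case against.** The strongest reply is that the article condenses a fuller protocol. It names no covariates or random effects, and an SAP that is not shown may supply them. It nowhere says that participants are treated as independent; that is inferred from the method named. This fully protects the 6-month analysis, because a linear mixed model could carry a group effect and nothing excludes it. It protects the 3-month analysis less. The method named there is ANCOVA, and adding a random group effect would replace that model rather than fill in its detail.

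A second reply is that the inflation is hypothetical and may be small. That stands in part. At ICC 0 there is none. Groups may also be well below eight: recruitment is planned from January 2022 to September 2023, about 21 months, and 100 exercise participants spread evenly is about 2.2 per fortnight. If groups really start that often, the 5.1% to 5.9% range is the relevant one. Conversely, trainers who lead several groups could add correlation.

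A reader might infer that standard errors are certainly too small and type I error certainly above 5%. The documents do not support this, because both depend on an ICC they do not give. A reader might also think that the step from 160 to 200 provides room for clustering. It does not: the Sample size section already assigns that step to 20% attrition. Nor does the article say that one trainer stays with a group throughout, or that group membership goes unrecorded. Trainers report attendance to the research team, so the link may already exist.

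**Conclusion.** The concern holds in conditional form and is limited to the 3-month primary ANCOVA. Followed as written, that analysis ignores clustering that exists in one arm only, and it is anti-conservative for any positive within-group correlation. Type I error is about 5.4% to 7% at an assumed ICC of 0.01 to 0.05 with eight analysed per group, about 6.5% at ICC 0.05 with about six, and below 6% with groups of 2.5 up to ICC 0.10.

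The sample size also states no allowance for clustering, but the consequence there is modest. The stated 160 exceeds the roughly 128 that its inputs require. With eight per group, that keeps power near 80% up to an ICC of about 0.05 with small-sample degrees of freedom, or 0.07 to 0.08 by normal approximation. These limits assume that 80 per arm are in fact analysed. The change should be made before analysis, because it bears on the primary p-value and costs little.

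**What to change.** - Keep the exercise-group and trainer identifiers in the analysis dataset.
- Make the primary 3-month analysis a baseline-adjusted partially nested mixed model: a random intercept for exercise group in the exercise arm only, each control as its own cluster, arm-specific residual variance, and Satterthwaite or Kenward-Roger degrees of freedom.
- State the assumed ICC and the expected group size in the sample-size section. Attribute any margin for clustering to 160 analysed over about 128 required, not to 200 over 160.

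The cost is a short change to the analysis text, identifiers that may already be held, slightly wider intervals and slightly lower stated power. At ICC 0 the simulated loss is about two points (88% to 86%). No extra patients are needed if the ICC is at or below about 0.05 with full groups. At ICC 0.10 with full groups, power would be 74% to 78%, and the plan should say so.
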